**Fortnightly 2-item survey for LifeBuoy+engagement arm only**

Hi, thanks for taking the time to answer these two questions!

| What the participant will see | | Response options |
| --- | --- | --- |
| Have you visited the Instagram page in the last 2-weeks? | --- select --- | No (0)  Yes (1) |
| Have you visited the Blog website in the last 2-weeks? | --- select --- | No (0)  Yes (1) |

# **Risk Management Protocol**

**Estimated flag and call-back rates**

Trial one, LifeBuoy study: 455 participants completed baseline; 259 were flagged (i.e., scored SIDAS >20); and 5/259 (1.93%) requested a call back from the team clinical psychologist.

**Flagging procedure**

**1)** At each survey timepoint (baseline, 30-days, 60-days, and 120-days) three items indicates risk of suicide. When a selection is made indicating a concerning level of suicidal thinking (SIDAS score >20), a suicide attempt during the trial, or NSSI requiring medical care during the trial, an automated alert system is triggered, where an automated email is sent to the participant asking if they would like to receive a phone call from the team clinical psychologist during business hours (9:00 to 17:00 AEST) within the next 3 working days. This email will also include a list of crisis contact numbers for support.

*“Hi there,*

*Thanks so much for signing up to participate in the study and for completing the latest survey. We noticed that your responses on the survey indicate a recent self-harm event or severe current suicidal thoughts. If you would like to receive a phone call from our clinical psychologist during business hours (9:00 to 17:00 AEST) within the next 3 working days, please click ‘reply’ to this email or send a new email request to [contact]*

*If you’ve had a tough time with your mental health lately, we encourage you to talk to a local doctor or mental health professional about how you’re feeling. If you would like to know where to get some immediate help, here are some suggestions:*

- *Lifeline: [name]*
- *Kids Helpline :[name]*
- *Suicide Callback Service: [name]*

*For 24-hour advice on what to do and who to contact, don’t hesitate to visit HealthDirect (https://www.healthdirect.gov.au) or call them at [name]).*

*If you feel in danger or that you might hurt yourself, do not hesitate to call Emergency Services on 000.*

*Warm regards*

*The LifeBuoy team”*

(*Note:* at the completion of each survey all participants will be shown a screen with the same abovementioned support contacts).

**2)** If a flagged participant indicates they would like a call back, the team clinical psychologist ([name]) will contact the participant via phone as soon as possible. This discussion will centre around making sure the young person is supported in their family and/or community and identifying how they can access the services they need. If the participant expresses distress in relation to using the app or answering the assessment questionnaires, they will be reminded of their right to withdraw from the trial without penalty or the need for explanation.

**3)** In the event that a participant does not answer the initial contact attempt, an email stating that contact was attempted and a request for their availability will be sent. The psychologist will attempt to call the participants up to two times in this allocated time. If the participant is still unavailable another email stating that contact was attempted, and containing referral sources, will be sent:

*“Hi <firstname>,*

*The team psychologist called you today between <time> as instructed by yourself, but you were not available. They will try up to two times to reach you – please note their call may show up as ‘unknown’ or ‘private’.*

*If you would like to know where to get some immediate help, here are some suggestions:*

- *Lifeline: [name]*
- *Kids Helpline :[name]*
- *Suicide Callback Service: [name]*

If you feel in danger or that you might hurt yourself, do not hesitate to call Emergency Services on 000.”

**4)** Details of these interactions will be recorded in a trial management risk spreadsheet, including failed attempts to contact the participant via telephone.

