**Safety Analyses**

Suicidal behaviour (ideation, attempts, and NSSI)

- Suicidal ideation, as measured by % scoring >20 on the SIDAS
- A suicide attempt during the trial identified at all follow up surveys: “Since the last LifeBuoy study survey, how many times have you made an attempt to kill yourself in which you had some intent to die?” >0 (T1 – T3) or ad hoc self-report by participants to research study email.
- Non-suicidal self-injury during the trial identified at all follow up surveys: “Since the last LifeBuoy study survey, how many times have you injured yourself on purpose without suicidal intent (i.e., intentional, self-inflicted damage to the surface of the body but with no intent to die)?” >0 (T1 – T3) or ad hoc self-report by participants to research study email.
- Serious adverse events (including all events requiring medical intervention).
- Enrolment data, intervention completion data, attrition data, adverse event data, and other administrative data.

The TSG cannot access the unblinded data for suicidal ideation, attempt, or NSSI as these are outcome measures and will be shared only in a closed session.

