**Trial Stopping Guidelines**

The DSMB has the responsibility for deciding whether the trial should be stopped at any stage. They will do this if, and only if, two conditions are satisfied:

1. The results provide proof beyond reasonable doubt that the intervention is on balance definitely harmful, or for a particular category of, participants in terms of the major outcome; or is on balance, definitely having a therapeutic effect (noting that this is extremely difficult to assess without long-term follow-up periods).
2. The TSG are not conducting the project safely, which would include, but is not limited to, a failure to contact participants who flag as ‘at risk’ (scores >20 on the SIDAS, suicide attempt during the trial, or NSSI requiring medical care during the trial) within the 48 hour period specified in the Duty of Care section within the Trial Protocol.

There is no plan to conduct any interim analyses, unless in cases where there is justification to unblind the data and condition (1) above is met. If this occurs, this DSMB Charter aligns with the Peto-Haybittle stopping rule whereby an interim analysis of a major endpoint would generally need to involve a difference between treatment and control of at least three standard errors to justify premature disclosure. An interim subgroup analysis would have to be even more extreme to justify disclosure. This rule has the advantage that the exact number and timing of interim analyses need not be pre-specified. In summary, the stopping rules require extreme differences to justify premature disclosure and involve an appropriate combination of mathematical stopping rules and scientific judgment.

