| (If 2 or 3) How many sessions have you had with your current mental health professional? | (free numerical response) | 0 to 1000 |
| What is the longest you have stayed with a mental health professional | --- select ---- | N/A  Less than a month (1)  1 to 3 months (2)  3 to 6 months (3)  6 to 12 months (4)  1 to 2 years (5)  More than 2 years (6) |

Now we’re going to ask you some questions about suicidal thoughts, and the severity of them. Please think about the past 30-days when answering the following questions.

[Suicidal Ideation Attributes Scale] (SIDAS)

| Question | Response options |
| --- | --- |
| In the past month, how often have you had thoughts about suicide? | 0 (Never), 1,2,3,4,5,6,7,8,9, 10 (Always) |
| In the past month, how much control have you had over these thoughts? | 10 (Full control), 9, 8, 7, 6, 5, 4, 3, 2, 1, 0 (No control) |
| In the past month, how close have you come to making a suicide attempt? | 0 (Not close at all), 1,2,3,4,5,6,7,8,9, 10 (Made an attempt) |
| In the past month, to what extent have you felt tormented by thoughts about suicide? | 0 (Not at all), 1,2,3,4,5,6,7,8,9, 10 (Extremely) |
| In the past month, how much have thoughts about suicide interfered with your ability to carry out daily activities, such as work, household tasks or social activities? | 0 (Not at all), 1,2,3,4,5,6,7,8,9, 10 (Extremely) |
| **Note:**Respondents who respond “0 – Never” to the first item skip all remaining items and score a total of zero. **Note:** item 2 is reverse scored.  **Scoring:** add total (range from 0 to 50) | |

We’d just like to ask you a few questions about prior self-harm thoughts and behaviours. Please look after yourself as you go through these questions and take breaks as needed.

[Other suicide-related questions] (Other_SI)

| What the user will see | | Drop down response options available |
| --- | --- | --- |
| How many times have you made an attempt to kill yourself in which you had some intent to die?  *Baseline only* | (free numerical response) | Participant to type in the number |
| (If >0) How many suicide attempts were made in the past 12 months?  *Baseline only* | (free numerical response) | Participant to type in the number |
| (If >0) How many suicide attempts were made in the past 30 days? | (free numerical response) | Participant to type in the number |

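### The baseline risk alert names three triggers, but two are worded as events within the trial, so as written only SIDAS above 20 can effectively fire at baseline

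*Protocol*

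**What the plan says.** The Flagging procedure opens with the timing: "At each survey timepoint (baseline, 30-days, 60-days, and 120-days) three items indicates risk of suicide". The next sentence lists the triggers for the automated email that offers a call from the team psychologist. They are a SIDAS score above 20, "a suicide attempt during the trial, or NSSI requiring medical care during the trial". The email tells the recipient that "your responses on the survey indicate a recent self-harm event or severe current suicidal thoughts".

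The DSMB Charter uses the same limit. Under Trial Stopping Guidelines, at-risk participants are those with "scores >20 on the SIDAS, suicide attempt during the trial, or NSSI requiring medical care during the trial". Under Safety Analyses, the two event types are tied to T1–T3: "A suicide attempt during the trial identified at all follow up surveys" and "Non-suicidal self-injury during the trial identified at all follow up surveys".

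The outcome surveys ask about suicide attempts in the past 30 days, self-injury in the past 30 days, and the care needed for the most severe episode of each. None of these items is marked as baseline only or follow-up only, so they belong to the baseline survey too.

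**The concern.** The two adjacent sentences do not fit together. The first gives all three items a role at baseline. The second confines two of them to a period that has barely begun at baseline. Consent and registration come before the baseline survey, so a short window exists, but no baseline question isolates it. A programmer could follow the trigger wording and let only SIDAS fire at baseline, or follow the timing sentence and use the 30-day answers.

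Under the first build, someone who discloses hospital-treated self-harm from the previous week at baseline, with SIDAS of 20 or below, gets only the general contacts screen. The same disclosure at T1 would bring the offer of a call. The protocol gives no reason for the difference. Such people can enrol: a recent attempt or self-injury is not an exclusion criterion, and the screening survey does not ask about it. Recruitment to baseline runs online without direct researcher contact, so this email is the only survey-triggered call offer described.

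**Working it through.** **1. The plan's own figure.** Under Estimated flag and call-back rates, 5 of 259 flagged participants in the earlier trial asked for a call: 5/259 = 1.93%, as stated.

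**2. Does SIDAS above 20 catch the same people anyway?** The scale has five items scored 0–10, total 0–50.

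- *Recent attempt, item 3 scored 10.* The alert is missed if the other four items (maximum 40) total 20 − 10 = 10 or less. With item 1 at least 1, the lowest possible total is 1 + 10 = 11. Of the 10 × 11 × 11 × 11 = 13,310 patterns for the other four items, 715 leave the total at 20 or below. This counts patterns and is not a probability. It shows that the gap exists and that most combinations fall outside it.
- *Item 1 answered as never.* Such respondents "to the first item skip all remaining items and score a total of zero", so no alert fires. Screening admits passive thoughts of being dead, so an eligible person could give this answer.
- *NSSI.* No SIDAS item asks about it. It need add nothing to the score, so the alert is missed at any total of 20 or below.

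SIDAS alone therefore does not fully stand in for the two event triggers, least of all for NSSI.

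**3. Illustration of size.** The protocol does not say how many people report a recent event with a low SIDAS score, so part of this rests on assumption.

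| Step | Calculation | Result |
|---|---|---|
| Not flagged on SIDAS, earlier trial | 455 − 259 | 196 |
| Share not flagged | 196/455 | 43.1% |
| Same share of planned enrolment | 0.431 × 669 | about 288 |
| Extra emails if 1% had a qualifying event (assumed) | 288 × 0.01 | 2.9 |
| Extra emails if 10% had one (assumed) | 288 × 0.10 | 28.8 |
| Calls at 1.93% uptake, lower end | 2.9 × 0.0193 | 0.06 |
| Calls at 1.93% uptake, upper end | 28.8 × 0.0193 | 0.56 |

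The table treats the 259 flags as baseline flags, although the protocol does not state their time point. The uptake figure comes from people flagged on SIDAS; uptake after recent self-harm may be higher.

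**The case against.** The strongest reply is that the intended scheme can be read from the rest of the protocol: SIDAS at every survey, event triggers at follow-up only. The safety section treats SIDAS above 20 at any time point as an expected adverse event, but counts attempts and medically treated NSSI as serious adverse events only at follow-up. The DSMB Charter limits both events to the trial in two places. The earlier trial's flags are described by SIDAS alone. On this view the opening sentence is loose and the triggers say what was meant. The email does not settle the matter, because one template serves all surveys and joins its two grounds with *or*. This argument largely stands as an account of intent. It means that the inconsistency could also be removed by stating that only SIDAS applies at baseline. It supplies no reason to withhold the call offer from people who have just disclosed recent self-harm.

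A reader might go further and infer that the trial will in fact miss these participants, or leave them without support. The documents do not show that. The alert configuration is not described, and a system keyed to the 30-day answers would fire at baseline. The Charter cites a Duty of Care section that does not appear under that name in the text at hand, so a rule there cannot be excluded. Everyone sees the crisis contacts after each survey, and in the two LifeBuoy arms the daily check-in directs low mood to a safety plan and crisis numbers. These safeguards do not replace the call offer, but they limit the harm.

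**Conclusion.** The point holds as a wording inconsistency with a safety consequence if the text is followed literally: at baseline, only SIDAS above 20 effectively produces a call offer. Those affected would be participants with a past-30-day attempt or medically treated NSSI and a SIDAS total of 20 or below. Their number is not derivable and is probably small. The 3–29 range rests on an assumed 1–10% event rate and on carrying over the earlier trial's flag share. No endpoint, analysis, sample size or serious adverse event count changes. The case for acting is that the correction is cheap and improves protection at entry to a self-guided trial; neither a shown failure nor a large number of people is claimed.

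**What to change.** In the Flagging procedure, word the two event triggers as: *a suicide attempt, or NSSI requiring medical care, in the past 30 days (baseline) or since the last survey (T1–T3)*. Configure the alert to match, and bring the at-risk definition under Trial Stopping Guidelines into line. If the sponsor prefers SIDAS alone at baseline, the protocol should say so and not list three items for that survey; that removes the inconsistency but leaves the gap in the call offer.

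The cost is one line in the risk protocol, a matching line in the Charter and the alert setting, using answers already collected at baseline. The downside is a few more automated emails and an occasional call, about 2 per 100 extra alerts at the earlier trial's rate.

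A separate matter, given no weight here: T2 to T3 spans 120 − 60 = 60 days, while the self-injury count and care items recall 30. Both would need since-last-survey wording for the follow-up NSSI trigger to cover that interval.

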**Outcomes Monitoring**

There will be two levels of monitoring of risk in this project. The first is the trial steering committee which will consist of the Chief Investigator ([name]) and research team listed on the ethics application, and the second level is the Data Monitoring Safety Board (DSMB) and this is the group that serious adverse events and reactions will be reported in to. The trial manager will record the number of notifications at each assessment in the Report for DSMB document and will notify the DSMB every 3-months on how many alerts were triggered, and what follow-up was carried out. They will record these in a Case Report spreadsheet (see Appendix B) which will be securely stored on the Institute’s UNSW server.

**Data Storage and Management**

The Black Dog Institute at the University of New South Wales (UNSW) will host the website and store the collected data. All collected data will be held on a secure server at BDI/UNSW and will only be available to researchers and staff working directly on the project.

Some data will be collected directly through the LifeBuoy app, which includes participants’ rating of each challenge and tool, and app usage information (such as time spent in the app, number of lessons accessed and completed). This information gets uploaded to Black Dog Institute servers when the phone is connected to Wi-Fi. Quantitative data will be analysed using SPSS software.
